## Abstract

**Background:** Falls affects one of three people after 65 years old, and it can lead to serious consequences. Scientific evidence point out that physical exercise is the most efficient way to prevent falls among older adults.

**Objective:** The main objective of this study is to determine if a social marketing program can increase the attendance rate of people aged 60 and over at group balance workshops.

**Methods:** This quasi-experimental multicenter study is being conducted in three French Regions (Loire, Haute-Loire and Rhône) over a period of 18 months. The Social Marketing Campaign will be done in three ways. Firstly, a Communication Campaign will take place in the two Test Areas but not in the Control Area. Secondly, flyers have been designed to be distributed by local partners. Finally, conferences for older people will be organized in the areas of intervention in order to reach the target audience for the program. The study will include people aged 60 and older who want to participate in the Balance Program.

**Results:** The Crédit Agricole Loire/Haute-Loire Foundation funded the study and the Jean Monnet University of Saint-Etienne reviewed it. The Ethics Committee of the University Teaching Hospital of Saint-Etienne approved and peer-reviewed it on September 6, 2019, under Reference Number IRBN622019/CHUSTE.

**Conclusion:** The results of this first study will demonstrate whether or not social marketing for promoting group balance workshops in the elderly will increase their attendanceship in adapted physical activity sessions, especially those that prevent falls.

**Clinical Trial Registration:**
https://clinicaltrials.gov/ct2/show/NCT04136938, identifier NCT04136938.

## Background

The global phenomenon of aging present several public health challenges.; namely the development of long term care, the creation of adapted environments for elderly (1). Projections show between 2015 and 2050, that the proportion of over-60-year-olds in the world population will increase from 12 to 22%, representing about 2 billion people (1). Life expectancy is increasing, and should be accompanied with the improvement of the quality of life through the preservation of functional activity, i.e., physical activity. It is important though to allow older adults to maintain their autonomy (2, 3).

Falls remain a significant source of morbidity in people aged 65 in one out of three in this age group (4). The association between PA and the risk of falling in elderly was recently evaluated by systematic review and meta-analysis. These analyses came out with the conclusion that the risk of being a recurrent faller (two or more self-reported falls over the follow-up period of 12–36 months) was 39% higher in older adults with the lowest levels of PA (5).

Therefore, physical activity may be the most effective method in preventing falls among older people (4, 6, 7). Meanwhile the interventions aimed at maintaining balance are the most effective to avoid loss of autonomy (4, 8). Obviously the programs based on the maintenance of the balance are the least expensive There is evidence that these balance-based programs can be cost-effective (9); They produce great health results and particularly improve the quality of the rest of participants life (4, 9, 10). A 2019 meta-analysis (4) confirmed and supported that physical activity is indeed one of the most effective techniques for reducing fall rates and risk of falling. In this meta-analysis, 108 randomized controlled trials were included, with 23,407 participants in 25 countries. Programs offering multiple types of exercise (balance, functional and resistance) reduced the rate of falls by 34% and the number of people who fell by 22%, according to the authors. When interventions offered different forms of physical activity, including balance exercises, the rate of falls, compared with the no-intervention groups, was reduced by 24%, and the number of people who had one or more falls by 13%.

However, although there now is unanimity over its practical usefulness, there are many barriers in getting the elderly to participate in any PA (11, 12). Indeed, some believe they are no longer able to do so because of a loss of physical capacity, while others find that sports is only for the young or healthy. All this is because of the little awareness of the tailored activities that exist (11–13). That maybe the reason why, sum all, only a small number of elder participate in PA for fall prevention (14, 15).

The Balance Workshops, such as those developed by the French Federation of Physical Education and Voluntary Gymnastics (FFPEVG), aim at preserving the balancing function and the autonomy of older people. They also aim at giving them confidence in their movements, reducing the psychological impact of falling, boosting their self-esteem and increasing their mobility. This Balance Program will last for 12 weeks, including ten sessions of group PA and two individual test sessions.

Through these sessions, the sports trainer, specialized in the approach, will engage them in various motor movements that involve the different components of balancing. Depending on the capacities of the various participants and the results obtained during the tests, the sports trainer will design educational approaches that address the different components of balancing. There is the fieldwork that consists of collecting information and managing the environment, finding a place, applying methods, which lead to loss and recovery of balance, carrying out activities for muscular, and kinesthetic strengthening, and exercises tied to walking (rhythm, frequency, overcoming obstacles). There is also a global approach to handling the matter of balance in the form of advice – this by including themes on aging well, such as the impact of drugs, food, and home improvement (16).

Introduced in 1971 by Kotler and Zaltman (17), social marketing is used extensively by health actors and researchers in several areas such as smoking prevention, promotion of healthy eating and physical activity (18–22). Alain Andreasen in 1995, defined social marketing as “*the adaptation of commercial marketing technologies to programs designed to influence the voluntary behavior of target audiences to improve their personal welfare and that of the society*” (23). Therefore, social marketing, intends to appropriate the principles and approaches of commercial marketing (market research, targeting and segmentation of the target audience, the 4Ps of marketing: product, place, price and promotion) particularly used by private companies to promote prevention programs (24). The Social Marketing method is based on seven benchmark criteria defined by researchers in the field (25–28), specifically including:

- Behavioral objective: Defining a behavioral change objective for the intended target audience is fundamental, especially for evaluating the effectiveness of an implemented program (29, 30) (i.e., to increase PA);- Formative research: understanding the target audience is based on conducting market research. Market research provides an in-depth understanding of the needs, desires, values and lifestyles of the target audience (31). The purpose of market research is to inform the planning, development and implementation of social marketing programs (32, 33);- Segmentation: Segmenting means creating homogeneous groups of individuals with identifiable similarities. These similarities can be, for example, place of residence, age, lifestyle or health status (34, 35);- Exchange: To induce individuals to change their behavior, it seems important to provide them with something in exchange. R. Bagozzi assumes that the exchange between several social actors (e.g., the target audience and the promoters of a prevention programme) involves a transfer of tangible or intangible objects (36);- Marketing Mix: Social marketers have therefore taken the “4Ps” concept from commercial marketing and adapted it (88, 89, 111): Product: the behavioral offer made to the target audience. The product involves intangible elements such as the adoption of an idea or behavior; Price: offering financial support mechanisms to address financial or psychological barriers to adopting the proposed behavior; Place: facilitating access to services or products that enable a change toward the proposed behavior; Promotion: promoting the behavior through the use of communication tools;- Competition: In social marketing, as in commercial marketing, practitioners need to be aware that there are sources of competition to the adoption of the proposed behavior (23, 30). The main source of competition is the tendency of the target audience to maintain their current behavior, especially when that behavior involves an addiction (tobacco, alcohol, drugs, etc.) (37).- Evaluation: An assessment of the program is carried out.

Social marketing principles for preventional intervention have been successfully used in various field, including smoking prevention, healthy eating promotion, alcoholism reduction, and physical activity promotion (13–15). Furthermore, these social marketing initiatives have been effective in various age groups, from adolescents (38), adults (39) to older adulsts (40).

Although this method has proven its worth in these other contexts, its use in getting older adults to take part in regular PA remains limited (41).

The main objective of this study is to determine whether associating a Social Marketing program would increase the attendance rate of people aged 60 and over in Group Balance Workshops.

The secondary objectives of this study are: (1) to increase the participation rate in the Balance Workshop sessions, (2) to increase the level of the quality of life of the participants, and (3) to increase the level of PA among the people participating in the study.

## Materials and Methods

### Design and Setting (Study Status)

This quasi-experimental multicenter study is being conducted in three French Regions (Loire, Haute-Loire and Rhône). The quasi-experimental model was decided upon in view of testing causal hypotheses. It is envisaged that the program will be evaluated using a set of indicators that have been predefined.

The distribution of participants between the two groups (Test and Control) was based on the choice of the study designers. A Comparison group that is as close as possible to the Test group in terms of initial characteristics will allow us to identify the outcomes in the case where the Social Marketing campaign is not implemented. This method will bring proof as to whether the program will be the cause of the differences in outcomes between the Test and Comparison groups.

The Loire and Haute-Loire Regions were selected for the campaign to promote the Balance Workshops against falls in the older population. This was because of the presence of our partners for the implementation of the study. The Rhône Region was selected, not as a Test, but as the Control Area (Figure 1).

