**Figure 1 F1:**
[figure not shown]
Test and control areas of the study.

The Social Marketing Campaign consists of three ways; firstly, by a Communication Campaign in the two Test Areas using advertisements developed and posted in the local print media. Secondly, flyers have been designed to be distributed by our local partners. Finally, conferences for older people will be organized in the test areas to reach the target audience for this program.

Finally, to encourage people to participate in this PA program, a gift card worth 20 € will be distributed to participants at registration. Then, a second gift card worth € 20 will be distributed to those who carry out at least 10 sessions out of the 12 offered. This study will last for 18 months. The study is underway and started in March 2020. The study flow-chart (Figure 2) summarize the study.

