### Evaluation of the Social Marketing Benchmark Criteria

The Table 1 present the definition and the evaluation of each social marketing benchmark criteria.

**Table 1 T1:** Definition and evaluation of each social marketing benchmark criteria.

**Social marketing steps**	**Définition**	**Evaluation**
Behavioral objective	Defining a behavioral change objective for the intended target audience is fundamental, especially for evaluating the effectiveness of an implemented program	Statistical analysis about an increase or not of PA participation and level
Formative research	Understanding the target audience is based on conducting market research. Market research provides an in-depth understanding of the needs, desires, values and lifestyles of the target audience. The purpose of market research is to inform the planning, development and implementation of social marketing programs	We did this step 1 year before the beginning of the study and allow us to build the research protocol.
Segmentation	Segmenting means creating homogeneous groups of individuals with identifiable similarities. These similarities can be, for example, place of residence, age, lifestyle or health status	Subgroup analysis, particularly by age group, will allow us to know if this segmentation criterion was effective. The qualitative survey of participants in the study areas (control and intervention) will allow us to know if there was any pollution of the study due to the geographical proximity of our territories.
Exchange	To induce individuals to change their behavior, it seems important to provide them with something in exchange. R. Bagozzi assumes that the exchange between several social actors (e.g., the target audience and the promoters of a prevention programme) involves a transfer of tangible or intangible objects (36);	An intervention territory will offer the workshops for 0€ and another territory for 20€. The evaluation of the level of participation by adjusting this parameter will allow us to evaluate the relevance of the free workshops.

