This study brings together a provider (the FFPEVG) and promoters (“Atout Prévention Rhône-Alpes” and ARSEPT Auvergne) which, in this case, are medico-social groups. Currently, the locations where the Balance Workshops take place belong neither to the provider nor to the promoters. To facilitate the setting up of these structures in our areas of intervention, we established collaborations with the City or Community Social Action Centers, which have rooms and gymnasia for such purposes. This joint collaboration between these various groups in these regions will provide a global solution to encourage older adults to move toward PA centered on balance.

Accessibility to the workshops, whether physical and/or financial, is an essential condition for the participation of older adults in these activities (52). This study will lead to the establishment of new workshops in all these areas of intervention, thus making the product more accessible to the target audience. Also, even if this Balance Workshop program is free in one region and costs very little in another, we wanted to offer incentives to be able to deepen our knowledge of their capacity or not to increase participation in our program.

The adaptation of the program to the needs and expectations of the older adults is also a condition that favors their participation (52). That is why we interviewed some of them to identify these issues and improve on our program. From the survey, we developed an intervention strategy that included appropriate communication with them (modification of communication tools and use of new media validated by them) and training of professionals with particular emphasis on the fears and expectations of their trainees.

We equally chose geographic segmentation. The Loire and Haute-Loire (Test) Regions will receive the marketing campaign, but not the Control Area (Rhône Region). These are neighboring Regions, so this introduces a bias in our study. Therefore, those who will run the program particularly in the Control Area, may have to make more efforts to increase participation in their workshops. Besides, local newspapers that are distinct for each area are being used to promote the workshops. However, these older adults move around; and so, some who live in the Control Area may become aware of the campaign and may want to participate in the workshops. There is therefore a risk of contamination of the study.

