Finally, though this study focuses on the evaluation of the whole intervention, stepwise evaluations will have to be carried out. For a start, an evaluation of the effectiveness of the campaign will be undertaken through the collection of data on the intention to participate in the study and to attend the workshops. Alongside, an economic evaluation will have to be done to know the most cost-effective and appropriate method of communication through which to encourage older adults to commit themselves to the program. A statistical evaluation will also have to be conducted to first of all highlight whether or not the campaign is more effective in the Test Area than in the Control Area. Then, in a second step, it will assess the evolution of the quality of life with PA levels as a function of exposure to the campaign. Lastly, a qualitative evaluation of the campaign will need to be carried out on the older adults and also on the actors in the field. This study will therefore evaluate the effectiveness of this Social Marketing approach and, if positive, will maximize the probability of the measures applied to be more sustainably adopted in the community.

However, this quasi-experimental model has some limitations. Just like for any technique applied only at the end of a program, the method can be significantly hampered by the lack of baseline data. Since such methods are based on certain causal assumptions, conclusions on causality are less pertinent/persuasive than those resulting from a randomized controlled trial.

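### The Methods promise proof of cause, but the campaign is allocated to whole areas with a single Control area, so the design can only estimate an area difference

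*Protocol article*

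**What the plan says.** All references are to the protocol article.

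- **Claim.** Design and Setting: "This method will bring proof as to whether the program will be the cause of the differences in outcomes". The conclusion of the Abstract and the closing Conclusion both say that the results will demonstrate whether social marketing raises attendance.
- **Allocation.** Design and Setting: "The distribution of participants between the two groups (Test and Control) was based on the choice of the study designers". On the choice of Loire and Haute-Loire as Test areas: "This was because of the presence of our partners for the implementation of the study". On the comparator: "The Rhône Region was selected, not as a Test, but as the Control Area".
- **Level of delivery.** The text after Figure 1 describes "a Communication Campaign in the two Test Areas using advertisements developed and posted in the local print media", together with flyers and conferences. The campaign is therefore given to areas, not to individuals.
- **Caveat.** The last paragraph of the Discussion says that "conclusions on causality are less pertinent/persuasive than those resulting from a randomized controlled trial", because such methods rest on causal assumptions. Separately, it mentions the lack of baseline data.

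**The concern.** The Methods and the Discussion make incompatible statements about what the study can conclude, and the stronger one stands in the Methods. With one Control area, the comparison of Test with Control is also a comparison of Rhône with two other places. A participant-level p-value or confidence interval reflects only the sampling of participants within those three areas. A significant difference would show that attendance in Rhône differs from attendance in Loire and Haute-Loire. It would not show why. The causal claim would go beyond the data even if every planned analysis were carried out perfectly.

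**Working it through.** **1. The plan's own figure.** Number of Participants Required gives π1 = 0.43, π2 = 0.63, α = 5%, power 90% and 105 per group. The pooled-variance formula, with mean proportion 0.53, is

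n = [z_α·√(2 × 0.53 × 0.47) + 1.282·√(0.43 × 0.57 + 0.63 × 0.37)]² / 0.20².

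- One-sided, z_α = 1.645: n = 104.8, so 105 per group and 210 in total. This matches.
- Two-sided, z_α = 1.960: n = 128.8, so 129 per group and 258 in total. This does not match.

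The article does not state sidedness, so both are carried below. The formula treats participants as independent and has no area term.

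**2. Area differences that the article itself documents.**

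- *Partners.* Their presence decided which areas became Test areas (Design and Setting).
- *Recruitment route.* In the Test areas, people who saw the advertisement contact the partners. In Rhône, the workshop provider contacts older people (the two Selection sections).
- *Fee.* Table 1, Exchange row: "An intervention territory will offer the workshops for 0€ and another territory for 20" euros. The Discussion also says that the programme is free in one region and low-cost in another. The second territory is not named.

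**3. Area-level degrees of freedom.** Three areas minus two arms leaves 1. It comes only from Loire against Haute-Loire and assumes that the same variance applies to Rhône. The two-sided 5% critical value of t on 1 df is 12.7, against 1.96 for the normal. If the fee separates Loire from Haute-Loire, that contrast also carries the fee and no clean degree of freedom remains. If the fee separates Rhône from a Test area, price is mixed with the campaign instead.

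**4. False positives of a participant-level test (illustration).** Assume no campaign effect, a common rate of 0.43, Test participants split equally between two areas, and an area SD τ. The article gives no τ, so a range is shown.

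- Sampling SE: √(2 × 0.43 × 0.57 / 105) = 6.83 points.
- Area contribution to the variance of the difference: τ²(1/2 + 1) = 1.5τ², an SD of 1.22τ.
- Ratio r = 6.83 / √(6.83² + 1.5τ²).
- Two-sided error: 2[1 − Φ(1.96r)]. One-sided error: 1 − Φ(1.645r).

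| τ (points) | SD of difference | r | Two-sided | One-sided |
|---|---|---|---|---|
| 0 | 6.83 | 1.000 | 5.0% | 5.0% |
| 2 | 7.26 | 0.941 | 6.5% | 6.1% |
| 5 | 9.18 | 0.745 | 14.4% | 11.0% |
| 10 | 14.02 | 0.487 | 34.0% | 21.1% |

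A simulation of 200,000 runs (Test areas 53 and 52, Control 105) gave two-sided rejection rates of 6.2%, 14.1% and 34.0% for τ = 2, 5 and 10. More participants shrink the 6.83 but leave 1.5τ² untouched.

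**5. What the 2018 rates say.** Loire 44% and Rhône 42% give an SD of 2/√2 = 1.4 points, hence r = 0.969 and a two-sided error of 5.7%. This is one contrast from one year, and no rate is given for Haute-Loire.

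**The case against.** The strongest reply is that much of this is already disclosed. The article calls itself quasi-experimental and states that the designers chose the groups. It admits bias and contamination from neighbouring areas, and it says that causal inference is weaker than in a randomised trial. The sentence at issue also follows an aim that the comparison group be as close as possible to the Test group at the start. A partner-dependent regional campaign will always have few areas. This stands as mitigation, and it makes the remedy a matter of wording. It does not remove the conflict, because the Methods still promise proof and nowhere does the article say that a single Control area leaves area variation out of the interval.

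Four stronger readings are tempting, and the documents do not support them.

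- *That area variation cannot be estimated at all.* There is at most one degree of freedom, which is very little but is not zero unless the fee splits the two Test areas.
- *That the Discussion blames only missing baseline data.* Its causality sentence gives its own reason, namely causal assumptions.
- *That the true error rate is 14% to 34%.* Those values need an area SD of 5 to 10 points and a two-sided test. The article states neither, and its only area data point to a small SD.
- *That venues, calendar or provider differ between arms.* The article does not show this. The same federation organises workshops in both arms, follow-up is described alike, and one data-collection period is given.

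**Conclusion.** The point holds as an overclaim built into the Methods. With "The Loire and Haute-Loire (Test) Regions will receive the marketing campaign, but not the Control Area (Rhône Region"), the campaign effect and the Rhône effect are one contrast, and no adjustment for participant characteristics or mixed model over workshops can pull them apart. The contradiction with the Discussion and the aliasing follow from the text alone. The numerical size does not: the excess over 5% runs from under 1 percentage point (two-sided, τ from the 2018 pair) to about 29 points (two-sided, τ = 10), under the assumptions in the working. The study can still yield a useful estimate of the difference between areas. Only the causal claim must be conditional.

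**What to change.** - In Design and Setting, replace the sentence that promises proof with: *The study will estimate the difference in attendance between areas with and without the campaign; a causal reading assumes no other area difference.* This brings it into line with the Discussion.
- In the conclusion of the Abstract and in the Conclusion, soften the statement that the results will demonstrate an effect so that it matches.
- With the primary result, state that the confidence interval excludes area-to-area variation. Its lower limit (where positive) is then also the size of area difference that would bring the interval to zero. For example, observed rates of exactly 43% and 63% would give a half-width of 1.96 × √[(0.43 × 0.57 + 0.63 × 0.37)/105] = 13.2 points and a lower limit of 6.8. No separate sensitivity figure is needed, since it would repeat that limit.

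The cost is a few sentences and a weaker headline claim. No additional data, areas or participants are required.
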